The radiographic appearance of the breast varies according to differences in the relative

distributions of fat and fibroglandular tissues. The extent of mammographically detected

fibroglandular breast tissue (i.e., percent breast density) is a strong breast cancer risk factor.

Although a large body of evidence shows consistent associations of percent breast density with age, reproductive factors, body mass index (BMI) and use of postmenopausal hormone replacement therapy (HRT), there are few data on associations of modifiable lifestyle factors with breast density. Results of some observational epidemiologic studies suggest that dietary vitamin D and calcium intake might be associated with a lower risk of breast cancer. In addition, other observational studies have shown inverse associations of vitamin D and calcium intake with percent breast density. It is possible that a protective effect of vitamin D on breast cancer etiology is mediated through vitamin D signaling effects on mammary epithelial cell differentiation, proliferation and apoptosis. Similarly, calcium also appears to exert anti-neoplastic effects.

The Vitamin D/Calcium Mammography Study is designed to assess the effects of supplemental vitamin D and calcium carbonate (and their synergistic effects) on mammographic breast density as an ancillary study of the Vitamin D/Calcium Polyp Prevention Trial. This multi-centered, randomized clinical trial provides an ideal opportunity to study the associations of vitamin D/calcium with breast density for several reasons. First, the primary exposures will be known quantities of vitamin D and calcium, thus removing the potential measurement errors introduced by dietary data collection. Second, we will be able to compare changes in density over time across the calcium only, vitamin D only, both or placebo groups. Third, the availability of high-quality data collected on potential confounding factors (e.g, hormone use, BMI, menopausal status, and age) will allow us to control for potential confounding factors that might differ between groups. Fourth, we are able to explore whether variants in genes in the vitamin D receptor might modify associations of supplemental vitamin D with percent breast density. If successful, the results of this study could be used to inform the design of a chemoprevention trial of vitamin D and/or calcium supplement to prevent breast cancer with percent breast density as the intermediate endpoint.

*10.5.2 Objectives*

The primary aim of this study is to assess the effects of supplemental vitamin D3 (1000 IU/daily) and calcium carbonate (1200 mg elemental calcium/day) on mammographic breast density.

Our primary hypotheses are:

1. Vitamin D3 (1000 IU/day) supplementation reduces mammographic breast density.

2. Calcium carbonate (1200 mg elemental calcium/day) supplementation reduces mammographic breast density.

Our secondary hypothesis is:

1. The combination of both vitamin D3 (1000 IU/day) and calcium carbonate (1200 mg elemental calcium/day) supplementation reduces mammographic breast density more than supplementation with calcium carbonate or vitamin D alone.

An exploratory hypothesis is:

1. The effect of supplementation with vitamin D3 on mammographic breast density will be modified by polymorphisms at the 3' end of the vitamin D receptor gene.

2. The combination of both vitamin D3 (1000 IU/day) and calcium carbonate (1200 mg elemental calcium/day) supplementation reduces mammographic breast density compared to placebo.

*10.5.3 Recruitment and Enrollment Procedures*

The parent study defines the pool of potential subjects for this study. Two *additional* exclusion criteria for this ancillary study are: a) a history of breast cancer, and b) not anticipating having a mammogram during the duration of the parent study. Subjects will be invited to participate in the Mammography Study in one of two ways:

1. Women currently being enrolled in the parent study will be invited to participate at the time of their in-person intake visit. Study coordinators will ask women to complete the mammography eligibility and intake questionnaire. Those who are eligible will be invited to participate in this ancillary study. If they are interested, the informed consent process will be carried out at this visit and documented on the informed consent form. The subject will also be asked to sign a medical release form to allow collection of their mammograms. Upon the subject’s randomization in the parent study, the study coordinator will collect the most recent screening mammogram from prior to enrollment, as well as subsequent mammograms from at least one year after enrollment into the parent study up until the end of the subject’s participation in the parent study. Subjects that consent to this ancillary study but become run-in failures in the parent study will be dropped from this study and their mammograms will not be collected.
2. Women already randomized into the parent study, will also be invited to participate. Study coordinators will ask women who are currently randomized in the study if they are interested in participating in the Mammography Study during an interim study visit (i.e. the year 1 blood draw), or during phone contact for an interval questionnaire. For interested and eligible subjects, local IRB procedures for obtaining informed consent will be followed. Where permissible, the informed consent process will be carried out over the phone and then documented by mailing an informed consent form and a release of medical information to the subject for their signature. Once the signed consent form is returned the study coordinators will collect the most recent screening mammogram from prior to enrollment, as well as subsequent mammograms from at least one year after enrollment in the parent study up until the end of the subject’s participation in the parent study.

*10.5.4 Collecting Mammogram Information*

Once a subject is enrolled in this ancillary study, the study coordinators will ask each woman a few questions regarding their screening mammography history, including information on where and when the most recent mammogram was conducted and whether she was taking medications containing female hormones, such as hormone replacement therapy or birth control, at the time the mammogram was performed. She will be asked to sign a release of medical information form to allow collection of one of the images taken at that mammogram. Similarly, at the time of the interval (semiannual) interview, women enrolled in this ancillary study will be asked if they had a recent screening mammogram and, if so, where and when that mammogram was performed.

At the time of a screening mammogram, four images are generally taken: craniocaudal and medio-lateral oblique images of each the right and left breast. For this study, we will request the left breast craniocaudal image if available. If that image is not available, we will request the right breast craniocaudal image.

At each study center, the study coordinators will request the screening mammogram from the appropriate clinics. It is likely that images from the screening mammogram might be obtained in one of three ways. First, if available, it would be preferable to have the image from a full-field digital mammography system. In this case, the image can be electronically transmitted to investigators at Northwestern University for the assessment of percent breast density. A second possibility is to have the mammogram digitized at the original institution and to transmit the digital image to Northwestern University. Using either of these two methods, it is possible to maintain confidentially by using only the parent study ID number and date of the mammogram to identify the image. The third possibility is that only a film screen mammogram is available from an institution that cannot digitize it. In this case, the study coordinator will place a label with the study ID over any identifying information (e.g., name) on the mammogram. The film mammogram will then be sent to Northwestern University where it will be scanned. The film will then be returned to the institution of origin.

At Northwestern University, a trained technician blinded to treatment status will determine the percent of breast fibroglandular density measured from the craniocaudal image. An automated analysis will be used to measure the quantity of fibroglandular tissue in the breast. This method consists of four steps for each digital image: 1) display of the digital mammogram, 2) determining the area of the entire breast (excluding lesion markers, nipple markers, and pectoralis major muscle along the chest wall), 3) determining a threshold signal value that determines the edges of fibroglandular regions, and 4) calculating the breast area (BA) and the fibroglandular tissue area (FA) within the breast area by summing the number of pixels within each region. Percent breast density, which is simply the ratio FA/BA x 100, will be calculated. Percent density provides a 2-dimensional quantitative estimate of breast density that has been shown to have high inter- and intra-reader reliability in selecting the threshold value and determining breast density in screen film mammography (SFM).

*10.5.5 Statistical Considerations*

**Study Design**

The goal of the parent study is to enroll 3000 total participants and to randomize 2400. Based on current recruitment rates, approximately 40% of the participants are women; therefore it is estimated that approximately 960 participants will be women. Of the women recruited we expect that 624 will be enrolled in the two-arm and 336 will be enrolled in the full-factorial study. Based on preliminary data that were collected from four study centers (NC, SC, GA and TX), it is estimated that at least 80% of women randomized will be eligible (i.e., no history of breast cancer) and will agree to participate in the mammography study.

|  | **Vitamin D** | **Calcium** | **Vit D and Calcium** | **Placebo** | **TOTAL** |
| --- | --- | --- | --- | --- | --- |
| Two-arm |  | 312 | 312 |  | 624 |
| Full-factorial | 84 | 84 | 84 | 84 | 336 |
| **Total randomized** | **84** | **396** | **396** | **84** | **960** |
| **No. of eligible women who agree to participate.** | **67** | **317** | **317** | **67** | **768** |

The design for this ancillary study is a 2 x 2 factorial design as follows:

|  | **Calcium - No** | **Calcium – Yes** | **TOTAL** |
| --- | --- | --- | --- |
| **Vitamin D – No** | 67 | 317 | 384 |
| **Vitamin D - Yes** | 67 | 317 | 384 |
| **TOTAL** | 134 | 634 | 768 |

**Statistical Analysis**

In preliminary analysis, we will ascertain the distribution of percent breast density to determine whether there are outliers or evidence of non-normality. If non-normality is indicated within any of the four study groups, then the density data will be log transformed before statistical analysis. Group differences in potential confounding variables are likely to be small due to the randomized nature of the study. However, we will examine descriptive statistics by treatment group for variables collected at baseline and at each follow-up visit, including demographics, hormone use, menopausal status, and BMI. We will compute means and standard deviations for continuous variables, medians and interquartile ranges for ordinal variables, and percentages by category for categorical variables. Potential group differences will be compared using analysis of variance (ANOVA) for continuous variables and chi-square tests for dichotomous or polychotomous variables. If group differences are observed, they will be included as covariates in analyses.

In this ancillary study, we are collecting the most recent mammogram prior to randomization as well as each mammogram post-randomization after being on study for at least one year and through the end of the study. The time from the pre-randomization mammogram to the first mammogram post-randomization is likely to vary among women. Therefore, to maximize a potential treatment effect, we will base our primary analysis on the mammogram where women have been on treatment for the longest period of time (i.e., a post-test comparison).

The primary method of statistical analysis for this ancillary study will be two-factor ANOVA or analysis of covariance (ANCOVA), to take advantage of the factorial nature of the design. This analysis will include a factor for Vitamin D (No, Yes), a factor for Calcium (No, Yes) and a Vitamin D x Calcium interaction term. The presence of a significant interaction will be assessed first and if the interaction term is statistically significant, and if this is due to the mean density for the combined Vitamin D + Calcium group being lower than the other three groups, then the secondary hypothesis will be supported and will show that both supplements synergistically reduce density more than each supplement alone. If the interaction term is not significant, then the marginal means in the factorial design will be tested using the main effect for vitamin D to test hypothesis 1, and the main effect for calcium to test hypothesis 2. (If the interaction term is significant, then main effects will still be tested, recognizing that there are differential effects). If group differences are observed, we will then conduct exploratory analyses to determine whether supplementation leads to a change in breast density (i.e., between pre-randomization mammogram and post-randomization mammogram). In addition, in exploratory analysis we will also use ANOVA to test the hypothesis that mammographic breast density is significantly lower in women randomized to the combination of vitamin D plus calcium compared to the placebo group.

We will also use ANOVA to test the exploratory hypothesis that the effect of supplementation with vitamin D on mammographic breast density is modified by polymorphisms at the 3' end of the vitamin D receptor gene. For this analysis, we will include a dichotomous variable to represent the presence or absence of the polymorphism, a dichotomous variable for vitamin D supplement (yes vs. no), and a cross-product term of these two variable. We will also include a dichotomous variable for calcium (yes vs. no) is in the above analyses calcium is found to be significantly associated with breast density.

Since all statistical tests are based on a priori hypotheses and are done within the context of the ANOVA or ANVOCA models, there will be no adjustment for multiple testing in either the analysis or sample size calculations.

**Power/Sample Size Considerations**.

Using a two-tailed test with an =0.05, and 80% power, we computed the minimal detectable difference in mean percent breast density for each of the comparisons as described for each of the primary and secondary aims below.

Primary Aim 1: Our first primary aim is to determine if supplementation with vitamin D reduces mammographic breast density. For this comparison of vitamin D versus no vitamin D we expect 384 (317 + 67) women per comparison group. This sample size will have 80% power to detect an effect size of 0.20, where effect size is defined as the mean difference in mammographic density between the vitamin D and no vitamin D groups, divided by the within group standard deviation (assumed to be the same for both groups). The units for the mean and standard deviation are percent breast density denoted by ‘%’. In a large cross-sectional study of primarily Caucasian women aged 40-93 years, percent breast density was determined by analyzing mammograms (Vachon et al, 2002). In that study, a standard deviation of 15% was observed. Given the similar age range of women in that study and our proposed study, we based our power estimates assuming a standard deviation of 15%. Therefore, the minimal detectable difference between the vitamin D groups is 3% (=.20 x 15).

Primary Aim 2: Our second primary aim is to determine if supplementation with calcium carbonate (calcium) reduces mammographic breast density. For this comparison of calcium versus no calcium, we expect 634 (317 + 317) women in the calcium group and 134 women (67 + 67) in the no calcium group. This sample size will have 80% power to detect an effect size of 0.27. Assuming a standard deviation of 15% for percent breast density, the detectable difference between the calcium groups is 4.0% (=.27 x 15).

Secondary Aim 1: Our secondary aim is to determine if supplementation with both vitamin D and calcium reduces mammographic breast density more than supplementation with calcium alone or with vitamin D alone. This vitamin D by calcium interaction reflects the vitamin D effect in the absence of calcium (67 vs 67 women) compared with the vitamin D effect in the presence of calcium (317 vs 317 women). These sample sizes will have 80% power to detect an effect size of 0.54. Here, effect size is defined as (vitamin D effect in the absence of calcium – vitamin D effect in the presence of calcium)/within group standard deviation (grouping is the 4 treatment combination groups and the standard deviation is assumed to be the same for the 4 groups). Assuming a standard deviation of 15% for percent breast density, there is 80% power to detect a vitamin D vs no vitamin D mean difference in the presence of calcium that is 8% higher than the vitamin D vs no vitamin D mean difference in the absence of calcium. For example, if the mean percent density in the 67 women not on vitamin D and not on calcium is 30%, and the mean percent density in the 67 women on vitamin D and not on calcium is 27% (vitamin D effect in the absence of calcium is 30 – 27 = 3%), and if the mean percent density in the 317 women not on vitamin D but on calcium is 26%, then there is 80% power to detect a mean percent density in the 317 women on vitamin D and on calcium of 15% (vitamin D effect in the presence of calcium is 26 – 3 – 8 = 15%).

10.6 *Kidney Function with Vitamin D/Calcium*

This sub-study will investigate the effect of vitamin D and calcium supplementation on measures of renal function and blood pressure.

Subjects in the parent study who consent to this ancillary study will undergo the following additional procedures at their end of treatment (EOT) visit (either Year 3 or Year 5 EOT):

- Urine collection for measuring microalbuminuria
- Blood pressure measurement
- An additional vial of blood will be collected for measuring markers of kidney function (see below)

In addition, creatinine and calcium measurements previously performed on all randomized subjects in the parent study at baseline, year 1, and year 3 (for subjects with a 5 year follow-up colonoscopy) will be used in these analyses. Creatinine and calcium measurements will also be performed on blood samples collected on all randomized subjects in the parent study at the Year 3 and Year 5 End-of-Treatment visits and used in these analyses.

*10.6.1 Background*

Chronic kidney disease (CKD), assessed by either the presence of microalbuminuria or decreased kidney function, affects over 23 million people in the United States and is associated with a high risk of hypertension, cardiovascular events, mortality and progression to end-stage renal disease. Known risk factors for kidney disease include the presence of high blood pressure, diabetes mellitus, dyslipidemia, non-white race and older age. Novel risk factors for kidney disease progression are continuously being identified, including low 25-hydroxyvitamin D (25(OH)D) levels and elevated serum phosphate and FGF-23 levels.[175-177](#_ENREF_175)

Animal studies suggest plausible mechanisms whereby low 25(OH)D levels and high phosphate levels may be harmful. Activated vitamin D, 1,25-dihydroxyvitamin D (1,25(OH)2D), suppresses renin biosynthesis in mice and vitamin D deficiency stimulates renin production.[178](#_ENREF_178) In different animal models, 1,25(OH)2D or its analogs reduced proteinuria levels, preserved glomerular podocyte structure, [179](#_ENREF_179) decreased levels of transforming growth factor β1, an inducer of renal fibrosis, and inhibited mesangial cell proliferation, a marker of renal injury. [180](#_ENREF_180) High phosphate levels in rats lead to worse kidney function.[181](#_ENREF_181) In the setting of kidney disease, vitamin D supplementation may lead to higher phosphate levels through increased gut absorption but calcium therapy can act as a phosphate binder in the gut and may prevent a rise in phosphate levels in those treated with vitamin D.

High blood pressure can be both a consequence of kidney disease and can independently cause kidney disease. Low vitamin D levels have been associated with the development of incident high blood pressure. [182](#_ENREF_182) Some trials of vitamin D therapy have noted lower blood pressures in the vitamin D treated group. [183-185](#_ENREF_183) However, these trials had small sample sizes and were not powered to evaluate changes in blood pressure.

Thus far, vitamin D and phosphate binding therapies have not yet been tested in a large randomized clinical trial powered to evaluate kidney disease outcomes. The Vitamin D/ Calcium Polyp Prevention Study is the ideal setting in which to test the effects of vitamin D and/or calcium on kidney function in a double blind, placebo controlled setting.

*10.6.2 Objectives*

The primary aim is to investigate the effect of calcium and/or vitamin D on the prevalence of microalbuminuria, a marker of kidney damage, at the end of 3 or 5 years of treatment with calcium and vitamin D, calcium alone or vitamin D alone versus placebo.

*Hypothesis: Vitamin D treatment will be associated with a lower prevalence of microalbuminuria.*

The secondary aims are as follows:

1. To evaluate the effects of calcium and/or vitamin D on blood pressure at the end of 3 or 5 years of treatment with calcium and vitamin D, calcium carbonate alone or vitamin D alone versus placebo.

*Hypothesis: Vitamin D therapy will be associated with significantly lower blood pressure.*

1. To evaluate the effects of calcium and/or vitamin D on kidney function as measured by serum creatinine measurements at baseline, year 1, year 3 and year 5 in all participants of the parent study with available creatinine measurements. Additional urine and serum markers of kidney function to be measured at the end of 3 to 5 years of treatment will include:
   1. Urine: markers of tubular damage including KIM-1 and NGAL
   2. Serum: creatinine (to be assayed at the lab used for baseline measurement),calcium and cystatin C, an additional marker of kidney function
   3. Serum: bone markers and other markers of kidney disease progression including serum phosphate, alkaline phosphatase, intact parathyroid hormone (PTH) and fibroblast growth factor-23 (FGF-23) levels.

*Hypothesis: Treatment with vitamin D and calcium will result in better kidney function compared to placebo*.

*10.6.3 Recruitment and Enrollment Procedures*

The parent study defines the pool of potential subjects and those subjects who are willing to participate will be consented at the in-person End-of-Treatment visit (which is part of the parent study procedures) prior to their 3-year or 5-year follow-up colonoscopy. Participants will be reimbursed $15 for their time and effort after completion of the specimen collection.

*10.6.4 Specimen/data Collection and Analysis*

10.6.4.a Urine collection

Subjects will be instructed on clean catch urine collection techniques and will be provided with a pre-labeled sterile container for urine collection. After they have completed the urine collection they will give the urine to the research coordinator for processing.

10.6.4.bBlood pressure measurement

An automatic Sphygmomanometer will be used to provide a uniform measurement of blood pressures. All staff will be trained in the proper procedure for blood pressure measurement.

10.6.4.c Blood collection

Additional blood samples will be collected for this sub-study while the participant is undergoing the Year 3 or Year 5 End-of-Treatment blood collection.

10.6.4.d Processing and Shipping

Specimens (aliquots of blood and urine) will be shipped from the Study Centers to the Clinical & Molecular Pharmacology Shared Resource Laboratory at the Dartmouth Coordinating Center. These specimens will then be batched and shipped to the Albert Einstein College of Medicine for analysis.

Urines

Urine samples will be promptly frozen at -20C or below pending transfer to a -70C freezer for storage until shipment to the Coordinating Center.

Bloods

Blood samples will be sent to local labs for analysis (creatinine) or promptly frozen at -20C or below pending transfer to a -70C freezer for storage until shipment to the Coordinating Center.

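### The mammography study's primary analysis does not pre-specify baseline breast density as a covariate, and its covariate rule admits variables measured after randomisation

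*Protocol*

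**What the plan says.** The points below are all in protocol section 10.5, and mainly in section 10.5.5.

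- **Data.** Sections 10.5.3 and 10.5.5 plan to collect each participant's latest screening mammogram from before the trial, and later mammograms taken after at least one year on study.
- **Outcome.** Because the interval between films will vary, and to maximise any treatment effect, the study will "base our primary analysis on the mammogram where women have been on treatment for the longest period of time (i.e., a post-test comparison".
- **Model.** The analysis is a two-way ANOVA or ANCOVA. The terms named are vitamin D, calcium and their interaction. Baseline density is not among them.
- **Role of the baseline film.** It is mentioned only for a later step, taken if the groups are found to differ: "we will then conduct exploratory analyses to determine whether supplementation leads to a change in breast density".
- **Covariates.** Groups are compared by ANOVA or chi-square tests on "variables collected at baseline and at each follow-up visit, including demographics, hormone use, menopausal status, and BMI". The rule that follows is: "If group differences are observed, they will be included as covariates in analyses".
- **Power.** The detectable differences use a two-sided 0.05 test, 80% power and an SD of 15 percentage points taken from a cross-sectional study. No baseline correlation enters.

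**The concern.** There are two separate problems, and they have different consequences.

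**Precision.** A woman's density before treatment is an obvious predictor of her density afterwards. If it is left out of the model, all the between-woman variance stays in the error term, and chance baseline differences between groups go uncorrected. The protocol's reason for the post-test analysis supports taking the last film as the outcome. It is no reason to leave the first film out of the model. It also fits poorly with section 10.5.1, which presents comparison of density changes over time as a strength of the design.

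**Validity.** The covariate rule does not distinguish values recorded before randomisation from values recorded after it. A follow-up variable that differs between randomised groups may differ because of treatment, and the rule brings it into the model exactly when that pattern appears. Section 10.5.1 names BMI and hormone therapy as consistent correlates of density, so these variables are related to the outcome. Conditioning on their follow-up values can remove part of a treatment effect or create a spurious one. Selecting covariates by tests of group difference also means the primary model is not fixed until the data have been seen.

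**Working it through.** **Inputs (section 10.5.5).** Two-sided alpha 0.05 and power 80%, so z = 1.960 + 0.842 = 2.802. SD = 15 points. For vitamin D: "For this comparison of vitamin D versus no vitamin D we expect 384 (317 + 67) women per comparison group". For calcium: "we expect 634 (317 + 317) women in the calcium group and 134 women (67 + 67) in the no calcium group". The interaction compares 67 vs 67 women with 317 vs 317.

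**Step 1: reproduce the protocol's figures.** Detectable difference = 2.802 × 15 × √(1/n₁ + 1/n₂).

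- Vitamin D: 2.802 × √(2/384) = 0.202 SD, or 3.03 points (stated: 0.20 SD, 3%).
- Calcium: 2.802 × √(1/134 + 1/634) = 0.266 SD, or 4.00 points (stated: 0.27 SD, 4.0%).
- Interaction: 2.802 × √(2/67 + 2/317) = 0.533 SD, or 7.99 points (stated: 0.54 SD, 8%).

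The stated figures reproduce. They are those of an analysis without baseline density.

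**Step 2: add baseline density.** If ρ is the correlation between baseline and follow-up density, the ANCOVA residual SD is 15 × √(1 − ρ²). Each detectable difference is multiplied by √(1 − ρ²), and the unadjusted analysis needs 1/(1 − ρ²) times as many women for the same precision. The protocol does not give ρ, so a wide range is shown. Power for a 3-point vitamin D difference is Φ(3 / (residual SD × √(2/384)) − 1.960).

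| Assumed ρ | Variance removed | Vitamin D (points) | Calcium (points) | Interaction (points) | Power for 3 points, vitamin D | Unadjusted n per group for equal precision |
|---|---|---|---|---|---|---|
| none | 0% | 3.03 | 4.00 | 7.99 | 0.79 | 384 |
| 0.3 | 9% | 2.89 | 3.81 | 7.62 | 0.83 | 422 |
| 0.5 | 25% | 2.63 | 3.46 | 6.92 | 0.89 | 512 |
| 0.7 | 51% | 2.17 | 2.85 | 5.71 | 0.97 | 753 |
| 0.8 | 64% | 1.82 | 2.40 | 4.79 | 0.996 | 1067 |
| 0.9 | 81% | 1.32 | 1.74 | 3.48 | >0.999 | 2021 |

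Example at ρ = 0.8: residual SD = 15 × √(1 − 0.64) = 9.0, and 2.802 × 9.0 × √(2/384) = 1.82.

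These are percentage-point figures on the untransformed scale. Section 10.5.5 allows a log transformation, in which case they would not apply directly.

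**Step 3: the covariate rule.** No arithmetic applies. Read together, the two sentences say that variables from baseline and from every follow-up visit are screened by group, and that those that differ become covariates. Nothing in section 10.5.5 limits the second sentence to baseline values.

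**The case against.** Several objections are fair, and they limit the point.

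- **ANCOVA is named and the list of screened variables is open**, so baseline density could enter if it turned out to be imbalanced. It would therefore be too strong to say that the plan shuts baseline density out of the primary analysis. The point that stands is that its entry is not pre-specified. Entry only on imbalance would forgo the precision gain whenever the groups happen to balance.
- **A reader might infer that every woman will have a baseline film.** The documents do not support this. The two added exclusions in section 10.5.3 are a history of breast cancer and no mammogram expected during the study. A prior mammogram is not required, and no limit is set on its age.
- **A reader might infer that a post-test comparison is biased.** For vitamin D, to which all these women are randomised, it is not. The loss is in precision.
- **A reader might take the gain as certain to be large.** It depends on a correlation that the protocol does not give. Mixed digital, digitised and scanned images, use of the right breast when the left image is unavailable, and varying intervals between films could all lower it. At 0.3 the gain is small.
- **The harm from follow-up covariates is not quantified.** Nothing in the protocol says these supplements alter BMI, hormone use or menopausal status, and section 10.5.5 expects group differences to be small. The rule is still avoidable and still permits the wrong kind of adjustment.
- **This is a separately consented ancillary study.** Nothing here touches the parent trial's adenoma endpoint.

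**Conclusion.** Both parts hold as matters of text. The primary analysis is a post-test comparison without baseline density as a pre-specified covariate, and the covariate rule selects on observed group differences and admits post-randomisation values.

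The first part is a loss of efficiency. The vitamin D detectable difference of 3.03 points would fall to between 2.89 and 1.32 points for an assumed correlation of 0.3 to 0.9. A quarter or more of the variance is removed only if the correlation is about 0.5 or higher. The second part is a possible bias whose size cannot be computed from the protocol.

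A reader might also infer that the power statement is wrong. It is not: the stated 3, 4.0 and 8 points are correct for the unadjusted analysis as planned. The fault lies in the choice of analysis. The change is worth making because it uses data already due to be collected, but its importance is confined to the mammography study.

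**What to change.** In section 10.5.5, or in the mammography study's analysis plan:

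1. Keep percent density on the last on-treatment mammogram as the outcome.
2. Keep the vitamin D, calcium and vitamin D × calcium terms. They are needed for the second primary hypothesis (calcium) and the secondary hypothesis (the combination).
3. Add baseline percent density to the primary ANCOVA, on the same scale as the outcome if that is log transformed.
4. Name any further covariates in advance and take them at baseline only, for example age, BMI, menopausal status and hormone use.
5. State a simple rule for women without a usable baseline film.
6. Delete covariate selection by tests of group difference. Report follow-up hormone use, menopausal status and BMI descriptively only.

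The cost is a change of wording. No further mammograms or data items are needed, and the sample size can stay as it is. The existing power figures can remain as the unadjusted case.
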